### Phylogenetic analysis of HPV 16 and HPV 18 LCR variants

For all HPV16- and HPV18-positive samples, a 730-bp fragment of the LCR region will be amplified (HPV 16 primer sets: 16-LCRs 5′–gCTTgTgTAACTATTgTgTCA–3′ and 16-LCR-as 5′–gCTTgTgTAACTATTgTgTCA–3′; HPV 18 primer sets: 18-LCRs 5′–ACCTgCCAAgCgTgTgCgTg–3′ and 18-LCR-as 5′–AggTgCCTgCggTgCCAgA–3′) [37,38]. The LCR multiple sequence alignment will be conducted using ClustalX [39]. Sequence editing will be carried out by means of BioEdit software [40] to compare the nucleotide sequences with those of reference strains obtained from the on-line database. Phylogenetic trees will be constructed using the MEGA package [41], and a bootstrap analysis [42] will be performed. HPV 16 variants will be classified into the four major phylogenetic branches: European (East Asia), Asian-American, African-1 and African-2, as described by Yamada et al. [43,44]. HPV 18 variants will be classified into two major phylogenetic branches: European (East Asia) and non-European (Asian-American, African-1, African-2).

### HPV 16 and HPV 18 escape mutants

For all HPV 16-positive samples, a 911-bp and 879-bp fragment of the L1 gene will be amplified (1° fragment: L1_16_1F 5′–ATgTCTCTTTggCTgCCTAg–3′ and L1_16_1R 5′–gCATCAgAggTAACCATAgAAC–3′; 2° fragment: L1_16_2F 5’-CTATggACTTTACTACATTACAggCTA-3’; L1_16_2R 5′–gTTTAgCAgTTgTAgAggTAgATgA–3′) [45]. The overlapping of the sequences obtained from the two amplified fragments will allow the analysis of the L1 gene (1498-bp).

For all HPV 18-positive samples, a 911-bp and 870-bp fragment of the L1 gene will be amplified (1° fragment: L1_18_1F 5′–ATggCTWTgTggCggCCTAg–3′ and L1_18_1R 5′–gAgTCAgAggTAACAATAgAgC–3′; 2° fragment: L1_18_2F 5′–CCAYggRCTTTAgTACATTgCAAgATA–3′ and L1_18_2R 5′–gTTTAgAAgACgTAgYggCAgATgg–3′) [45]. The overlapping of the sequences will allow the analysis of the L1 gene (1489-bp).

Phylogenetic analysis of the sequences will be conducted by the bioinformatics programs described above. The analysis of codon-specific non-synonymous and synonymous substitutions and the selection pressures will be inferred by MEGA [41] and the Datamonkey facility [46].

### Bio-bank

Residual biological samples collected in the PreservCyt solution that are positive for HPV DNA and/or for cytological abnormalities will be stored at −20 °C for further studies. Concordant HPV DNA-negative/cytology-negative samples and residual urine samples will be processed as follows: after centrifugation, the pellet obtained will be stored at −20 °C and will then be available for future molecular investigations

### Variables to be analysed and data security

Descriptive statistics (means ± SD or median) and frequency analyses will be used to describe the whole study sample and each cohort with regard to demographic, epidemiological, behavioural, clinical, immunological, and HPV vaccination status data. Data will be collected with a specially developed e-CRF released on a web platform built with PHP 5.3 and JQuery. The database resides on MySql 5.0. The application is hosted at the Mario Negri Institute (99% uptime guaranteed, according to the service level agreement) with security features according to the current laws. Anonymous data extraction will be performed at the data storage centre.

### Statistical analyses

#### *Cross-sectional study*

Overall and HPV type-specific prevalence will be estimated with 95% confidence intervals (CI), according to the Poisson approximation, in the four participant groups (three high-risk groups and control group). Logistic regression models will be used to estimates odds ratios (OR) and their corresponding 95% CI to quantify the associations between HPV infection and major demographic, clinical and behavioural characteristics in the four participant groups. All variables will be analysed in both univariate and multivariate models to control for major confounding factors.

Sensitivity, specificity, and positive and negative predictive values of the HPV test compared with the Pap test will be estimated overall and by group. Test performance in matched pairs will be estimated with McNemar’s tests, and proportions will be compared using Fisher’s exact tests. Exact methods will be applied when expected cell frequencies are less than five.

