#### *Testing arms*

One thousand HIV-infected women (HIVW) will be recruited from those followed up for HIV infection in three infectious disease units. One thousand recent migrant women (less than 1 year) (RMW) will be recruited mostly through a faith-based organization, and 3000 young women (aged 13–26 years) will be recruited from those asking for a Gynaecologic (1326G) or Paediatric consultation (1318P). Those vaccinated with anti-HPV vaccines prior to enrolment or during the follow-up period will not be excluded from the study. Instead, the vaccinated participants will be considered a subgroup to be monitored and evaluated over time.

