#### *Power calculation*

The sample size was calculated by taking published data as well as economic feasibility into account to allow the estimation of differences in the prevalence of type-specific HPV between the high-risk and control groups. From preliminary results obtained from the first 1300 women enrolled (717 SPSW, 290 HIVW, 160 RMW and 133 1326 G), the prevalence varied from 0.5%–2% (for major high-risk HPV genotypes: 16, 18, 31, 51, 52, 53) in the control group, and was 2–3 fold higher in the high-risk groups (for HPV 16, 31, 51, 52, 53). The planed sample of 1000 women for each high-risk group and 2000 low-risk women will be adequate to detect differences for genotypes with a prevalence of 1%–1.5% in the control group.

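### Poisson-approximation intervals are prescribed for overall HPV prevalence, a binomial proportion; they are too wide by 1/√(1−p), which matters only if overall prevalence is high

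*Protocol article*

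**What the plan says.** Under Statistical analyses, Cross-sectional study, one interval method is fixed for both kinds of prevalence: "Overall and HPV type-specific prevalence will be estimated with 95% confidence intervals (CI), according to the Poisson approximation". The sentence goes on to apply it to all four groups. The same section has a clause on exact methods, but it applies when expected cell counts fall below five and follows the sentences on test comparisons. It does not change the interval for a common outcome.

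The only prevalence figures are in the Power calculation section, and they are for single genotypes. In controls, "the prevalence varied from 0.5%–2% (for major high-risk HPV genotypes: 16, 18, 31, 51, 52, 53) in the control group". The corresponding figure "was 2–3 fold higher in the high-risk groups (for HPV 16, 31, 51, 52, 53"). No any-type prevalence is given for any group. The planned sizes are given there as "The planed sample of 1000 women for each high-risk group and 2000 low-risk women"; the Testing arms section adds that "3000 young women (aged 13–26 years) will be recruited".

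**The concern.** The Poisson approximation to a binomial count is sound when the event is rare. The plan's single-genotype figures are in that range. Overall prevalence pools every type: the HPV genotyping section lists 28 on the panel, and the HPV X section adds samples that the panel cannot type. It must be at least as high as the commonest single type and may be much higher, yet it gets the same rare-event interval.

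The Methods/design section gives the estimation of HPV prevalence as a purpose of the cross-sectional study, and the Abstract lists overall prevalence among the estimates. An interval labelled 95% that covers more than 95% is mislabelled and understates the precision actually achieved.

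**Working it through.** The article states no interval width or precision target, so there is no figure of its own to reproduce.

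**Inputs from the article**
- Confidence level 95%, z = 1.96 (Cross-sectional study).
- n = 1000 for HIV-infected women and for recent migrant women (Power calculation). The width ratio below does not depend on n.
- Control prevalence per genotype 0.5%–2%, and 2–3 times that in the high-risk groups for HPV 16, 31, 51, 52 and 53 (Power calculation). This gives 2 × 0.5% = 1% up to 3 × 2% = 6% per genotype.

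**Formulas**
- Poisson half-width: 1.96 × √(p/n).
- Binomial half-width: 1.96 × √(p(1−p)/n).
- Ratio: 1/√(1−p).
- Approximate coverage of the nominal 95% Poisson interval: 2Φ(1.96/√(1−p)) − 1.

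**What the article's figures imply for the five named genotypes together, high-risk groups**
- Independent: 1 − 0.99⁵ = 4.9% up to 1 − 0.94⁵ = 26.6%, that is about 5%–27%.
- Complete overlap: 1%–6%.
- No overlap: 5 × 1% = 5% up to 5 × 6% = 30%.

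The ends of these ranges put all five genotypes at the same extreme, so they are outer limits for these five. HPV 18, the other 22 panel types and untypeable HPV come on top, by an amount that the article does not give.

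**Controls, six named genotypes, independent:** 1 − 0.995⁶ = 3.0% up to 1 − 0.98⁶ = 11.4%. The ratio is 1.015 to 1.06.

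**Results at n = 1000 (half-widths in percentage points)**

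| p | Basis | Poisson | Binomial | Ratio | Coverage |
|---|---|---|---|---|---|
| 0.5% | single genotype, low end | 0.44 | 0.44 | 1.003 | 95.1% |
| 6% | single genotype, high end | 1.52 | 1.47 | 1.03 | 95.7% |
| 4.9% | five genotypes, low end | 1.37 | 1.34 | 1.03 | 95.6% |
| 26.6% | five genotypes, high end | 3.20 | 2.74 | 1.17 | 97.8% |
| 30% | assumed | 3.39 | 2.84 | 1.20 | 98.1% |
| 40% | assumed | 3.92 | 3.04 | 1.29 | 98.9% |

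Exact limits give the same picture. At an assumed 40%, exact Poisson is 36.2%–44.1% and exact binomial (Clopper-Pearson) is 37.0%–43.1%, a width ratio of 1.288.

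**The case against.** The strongest reply is that the consequence is small and its size is not documented. Several parts of that reply stand.

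- No overall prevalence is given for any group. The Prospective study section provides for multiple infections, so single-type figures cannot simply be added.
- In absolute terms the difference is small. At n = 1000 and 26.6% it is 3.20 − 2.74 = 0.46 percentage points of half-width. For controls (n = 2000) at 10% it is 1.39 − 1.31 = 0.08 points.
- The error is on the conservative side, and nothing inferential rests on it. Associations use logistic regression, test comparisons use McNemar and Fisher, and the sample size rests on type-specific differences.
- The preliminary data (717 + 290 + 160 + 133 = 1300 women) include no paediatric participants. The Prospective study section plans about 250 girls per year of age from 13 to 18, roughly 6 × 250 = 1500. For them there is no figure from which to judge whether infection is common.

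What does not stand is any suggestion that the article already corrects the method. The small-cell clause deals with the opposite situation, and the Poisson method is expressly applied to overall prevalence.

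**Conclusion.** The point holds as a minor technical error. The stated method does not fit overall prevalence: the interval is too wide by 1/√(1−p) at any sample size. On the article's own figures, and assuming that the five named genotypes are independent, this means about 3%–17% excess width and about 95.6%–97.8% coverage in the high-risk groups. If the remaining types bring overall prevalence to 30%–40%, which is an assumption, the excess is 20%–29% and coverage about 98%–99%. Type-specific intervals are practically unaffected.

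A reader might infer more, in three ways that the article does not support:
- That infection is known to be common in the high-risk groups. This is an inference from single-genotype figures; any-type prevalence is not reported.
- That coverage is well over 95% throughout, or that the study in effect discards 40% of its women. The latter describes the width of one descriptive interval at an assumed 40% prevalence. No data or power are lost.
- That group comparisons or the sample size are compromised. Neither uses this interval, and the point estimates are unbiased.

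**What to change.** In the Cross-sectional study section, replace the Poisson approximation with Wilson binomial 95% intervals for overall and stratified prevalence. Wilson is preferable to the exact binomial interval, which is itself conservative. Using Wilson for type-specific prevalence as well is optional: it would give one method throughout and change those widths by no more than about 3%.

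The cost is one sentence. The interval needs only the number positive and the number tested, so no new data are required, and no other analysis or design quantity changes.

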**Methods/design:**

VALHIDATE is a 5-year multicentre open prospective cohort study. It will recruit 7000 consenting women aged 13–65 years to provide information about the local biomolecular epidemiology of HPV infection and cervical diseases in high-risk women recruited from nine clinical centres and one faith-based organisation. The study will estimate the overall and type-specific prevalence of HPV infection and cervical abnormalities. It also aims to compare standard Pap screening with biomolecular screening, and to assist in the design of targeted regional prevention programs directed specifically at high-risk groups. Three groups of high-risk women: 1000 HIV-infected women (aged 26–65 years), 1000 recent migrant women (aged 26–65 years) and 3000 young women (aged 13–26 years) and 1 control group: 2000 women (aged 26–45 years) attending a spontaneous screening program, will be recruited. Sample sizes will be revised after the first year. Adult participants will undergo conventional cervical cytology, HPV DNA screening and genotyping. Paediatric participants will undergo HPV DNA testing and genotyping of urine samples. HPV DNA, cytological abnormalities and HPV types will be analysed according to demographic, epidemiological, behavioural, and clinical data collected in an electronic case report form. Overall and stratified prevalences will be estimated to analyse the associations between HPV infection and selected characteristics. Logistic regression models will be used to estimate crude and adjusted odds ratios. Cox proportional hazard models will be used to estimate hazard ratios over time and between groups.

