### Baseline evaluation and follow-up

Adult participants will undergo a medical assessment appropriate to their group (gynaecologic evaluation, and infectious disease evaluation for HIV-infected participants), cytological screening following the Italian Guidelines [31] for Cervical Cancer or algorithms modified for HIV-infected women, and HPV DNA testing. Colposcopy referral will be driven by cytology results. The conventional Pap smears will be evaluated according to the 2001 Bethesda System by four pathology laboratories.

HPV-DNA testing will be performed by the reference virology laboratory. HPV DNA-positive samples will be genotyped using a commercial kit in the four microbiology laboratories. Oncogenic risk associated with HPV types will be defined according to the 2011 IARC classification [32]. Samples with a positive HPV DNA test but with genotypes not included in the InnoLipa panel will be typed by the restriction fragments length polymorphism (RFLP) technique in the reference virology laboratory. In this reference laboratory, HPV 16- and HPV 18-positive cervical brushes or urine samples will be further subjected to a phylogenetic analysis to study the circulation of variants belonging to different geographical clusters (European and non-European).

An additional analysis for the characterization of HPV 16 and HPV 18 variants that could potentially elude the immune response induced by the vaccination (escape mutants) will be performed.

Participants with discordant results (HPV-positive/cytology-negative) will be recalled after 12 months for reassessment with cytology and HPV testing.

Paediatric participants will undergo a paediatric evaluation and HPV DNA testing of urine samples. The algorithms for the follow-up of adult and paediatric participants are presented in Figure 1, Figure 2, Figure 3, and Figure 4. All data collected during the visits and derived from cytology and biomolecular evaluations will be recorded on a specially developed secure electronic case report form (eCRF).

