**Figure 4 F4:**
[figure not shown]
**Algorithm for the screening and follow-up of 1318P.** 1318P: young girls aged 13–18 years asking for a paediatric assessment of any health problem. HPV testing: Nucleic acid extraction from cervical samples (by NucliSENS*®* EasyMAG™, bioMérieux bv, France) followed by PCR amplification of a 450-base pair fragment of ORF L1 using the degenerate primer pair ELSI-f and ELSI-r.

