#### *Prospective study*

We will analyze the incidence of new cytological abnormalities, progression or regression of baseline lesions, incidence, clearance and persistence of HPV infection for all women who had at least one follow-up visit. The proportion of women lost to follow-up is expected to be different in each participant group. The RMW group may have more difficulty in returning for a follow-up visit. Socio-demographic differences between women who return and who are lost to follow-up will be analysed. Conversely, women in the HIV cohort, who will be recruited from the centre they attend for HIV treatment, may be more likely to attend the study follow-up visits.

The proportions of women who we expect to be lost to follow-up are therefore estimated at around 10%, 20% and 60% in the HIVW, SPSW and RMW groups, respectively.

Single and multiple infections will be defined without considering uncharacterized HPV types (HPV X). The Kaplan-Meier method will be used to evaluate differences in the incidence of abnormal cytology at follow-up between women in the high-risk groups versus the control group. When appropriate, a Cox model will be used to account for the effects of major confounding factors. For the paediatric group, we will recruit about 250 girls for each year of age between 13 and 18 years to estimate the age at first HPV infection, time to clearance or persistence of HPV infection, and the change after 3 years of follow-up related to major behavioural characteristics.

All the analyses will be performed using SAS software for Windows version 9.2 (SAS Institute Inc., Cary).

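### The young-women group pools urine-tested paediatric girls with cervically sampled gynaecology attenders, so its prevalence and its contrast with controls mix specimen and referral route

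*Protocol article*

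**What the plan says.** The Abstract (Methods/design) lists "Three groups of high-risk women: 1000 HIV-infected women (aged 26–65 years), 1000 recent migrant women (aged 26–65 years) and 3000 young women", plus one control group. The Testing arms section states that "3000 young women (aged 13–26 years) will be recruited from those asking for a Gynaecologic (1326G) or Paediatric consultation (1318P"). The Cross-sectional study section then estimates overall and type-specific prevalence "in the four participant groups (three high-risk groups and control group"), and fits its logistic models in the same four groups.

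On specimens, the Baseline evaluation and follow-up section says: "Paediatric participants will undergo a paediatric evaluation and HPV DNA testing of urine samples". The Abstract agrees: "Paediatric participants will undergo HPV DNA testing and genotyping of urine samples". The legends of Figures 1 and 3 give cervical samples for the controls (SPSW) and for 1326G. The legend of Figure 4, which covers 1318P, also reads "HPV testing: Nucleic acid extraction from cervical samples", which conflicts with the two urine statements.

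On size, the Prospective study section says of the paediatric group that "we will recruit about 250 girls for each year of age between 13 and 18 years". The Power calculation section sizes the study for differences in type-specific prevalence between the high-risk groups and the controls.

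**The concern.** Three high-risk groups plus one control group make four only if 1326G and 1318P are merged. The merged group then contains two specimens with different collection and processing, and two routes of entry: girls and women seeking gynaecological care, and girls brought to a paediatric clinic for any health problem. The protocol nowhere claims that urine and cervical samples detect HPV equally well.

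A single prevalence for this group is a weighted average whose weights are set by how many participants each clinic type recruits. A different split would give a different answer from the same underlying infection rates. When that average is set against controls who all gave cervical samples, a true excess in one stream can be diluted by lower detection, lower exposure, or both, in the other. The result is meant to inform regional prevention policy for young women, including whether vaccination is extended to other age groups.

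**Working it through.** **1. Share of the group tested on urine.** Inputs: about 250 girls per year of age (Prospective study) and 3000 young women in total (Testing arms).
- Ages 13 to 18 inclusive: 250 × 6 = 1500, and 1500/3000 = 50%.
- Age 18 not counted: 250 × 5 = 1250, and 1250/3000 = 42%.
- The remainder, 1326G, is 1500 to 1750.

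**2. Can adjustment separate specimen from stream?** Every 1318P girl gives urine, every 1326G participant gives a cervical sample, and no control gives urine. Within the young group, an indicator for specimen is the same variable as an indicator for stream, so its coefficient carries specimen, referral route and any remaining age difference together. The contrast of 1318P with controls has the same problem. The models name demographic, clinical and behavioural characteristics, but adding specimen to that list would not help.

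**3. Size of the dilution.** The documents give no sensitivity of urine relative to a cervical sample, so u is an assumption. With urine share w and true prevalences pG (1326G) and pP (1318P):
- observed = (1 − w)·pG + w·u·pP
- relative loss due to specimen = w(1 − u)·pP / [(1 − w)·pG + w·pP]

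If pG = pP, the loss is w(1 − u). For u = 0.9 to 0.6:
- w = 0.50: 5% to 20%; a true 2-fold ratio to controls appears as 1.9 to 1.6.
- w = 0.417: 4% to 17%; a true 2-fold ratio appears as 1.92 to 1.67.

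If prevalence is lower in 1318P, the specimen part shrinks. Illustration (assumed): pG = 20%, pP = 5%, u = 0.6, w = 0.5. The true pooled value is 12.5% and the observed value is (20 + 0.6 × 5)/2 = 11.5%, a loss of 1/12.5 = 8%.

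Lower prevalence also dilutes the pooled figure by itself. With u = 1, w = 0.5, 1326G at twice the control level and 1318P at the control level, the pooled ratio is (2 + 1)/2 = 1.5.

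**4. What splitting the streams costs in power.** The Power calculation section states no alpha and no power, so there is no figure to reproduce. I assumed a two-sided 5% test of two proportions (pooled variance, no continuity correction) and a 2-fold difference from 2000 controls.

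| Comparison with 2000 controls | Control prevalence 1% | Control prevalence 1.5% |
|---|---|---|
| 1000 per high-risk group, as stated | 60.3% | 76.5% |
| 1326G alone, 1500 | 68.6% | 84.7% |
| 1326G alone, 1750 | 71.5% | 87.3% |
| Pooled 3000, u = 1 | 80.4% | 93.7% |
| Pooled 3000, half urine, u = 0.8 | 63.9% | 81.9% |
| Pooled 3000, half urine, u = 0.6 | 43.1% | 60.1% |

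The pooled rows assume equal true prevalence in the two streams. On that assumption, pooling loses its power advantage over 1500 cervically sampled women by u = 0.8. For a 3-fold difference, 1500 women give 98.7% and 99.9%.

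**5. Basis of the sizing.** The preliminary data in the Power calculation section list 717 SPSW, 290 HIVW, 160 RMW and 133 1326G, and no 1318P. The observed 2- to 3-fold excess therefore contains no urine results.

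**The case against.** The best counter-argument is that the four groups may not include 1318P at all. The preliminary enrolment list has exactly four groups, all cervically sampled. The sizing speaks of 1000 per high-risk group, which does not fit a pooled 3000. The Prospective study section gives the paediatric girls their own recruitment target and questions, and Figures 3 and 4 give the two streams separate algorithms. The Abstract also promises stratified prevalences.

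This shows that the protocol separates the streams for some purposes. It does not outweigh the explicit definitions in the Abstract and Testing arms, where the 3000 young women are one of three high-risk groups. An interim list does not redefine the groups, the strata are not named, and no sentence keeps 1318P out of the four groups or out of the comparison with controls.

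A reader might also infer four stronger points that the text does not support:
- **A young-versus-control odds ratio is planned and biased.** The Cross-sectional study section specifies odds ratios for participant characteristics within the groups. The comparison with controls comes from the Power calculation section and concerns differences in prevalence.
- **The Pap comparisons fail for half the group.** They use matched pairs, so by construction only those with both tests enter. This calls for a clarifying sentence only.
- **The prevalence will be 5% to 20% too low.** That range needs an assumed urine sensitivity and equal true prevalence in both streams; the documents supply neither.
- **The split is fixed at 1500 and 1500.** It is derived from an approximate target, and the Abstract says sample sizes will be revisited after the first year.

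The Figure 4 legend could be read as showing that 1318P is cervically sampled after all. The Abstract, the Baseline evaluation section and the urine-handling text all point to urine, and the legend repeats the wording of Figures 1 to 3. Even on that reading, the mixing of referral routes would remain.

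**Conclusion.** The point holds. Followed as written, the plan gives one prevalence for young women in which about 42% to 50% of participants are urine-tested paediatric attenders, and sets it against controls who are all cervically sampled. Specimen and stream coincide completely, so modelling cannot undo this; only separate reporting can.

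The structural defect rests on the protocol's own definitions. Its numerical effect is unknown. The 5% to 20% relative shortfall is an illustration that depends on u = 0.6 to 0.9, equal true prevalence and a 50% urine share. If 1318P prevalence is lower, the specimen part is smaller, but the lower prevalence itself also pulls the pooled estimate down. This should be corrected before analysis. It does not affect the HIVW or RMW comparisons.

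**What to change.** - In the Cross-sectional study section, name five groups: SPSW, HIVW, RMW, 1326G and 1318P. Estimate prevalence and fit the models separately for 1326G and 1318P.
- Restrict prevalence comparisons with SPSW to the cervically sampled groups: HIVW, RMW and 1326G.
- Report 1318P separately, labelled as urine HPV prevalence, by year of age.
- State that the HPV-versus-Pap analyses exclude 1318P.
- Reconcile the Figure 4 legend with the Abstract and the Baseline evaluation and follow-up section, so that the specimen for 1318P is stated consistently. The Abbreviations list, which calls the paediatric stream 1326P aged 13–26, should be reconciled at the same time.

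The cost is wording and table layout; no data collection changes. The young group's sample for comparison with controls falls from 3000 to about 1500 to 1750. That is still above the 1000 per high-risk group in the Power calculation section, with higher power for a 2-fold difference than that design under the same assumptions.
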